## Abstract

**Background:**

Antiretroviral therapy (ART) has led to dramatic improvements in survival for people living with HIV, but is unable to cure infection, or induce viral control off therapy. Designing intervention trials with novel agents with the potential to confer a period of HIV remission without ART remains a key scientific and community goal. We detail the rationale, design, and outcomes of a randomised, placebo-controlled trial of two HIV-specific long-acting broadly neutralising antibodies (bNAbs): 3BNC117-LS and 10-1074-LS, which target CD4 binding site and V3 loop respectively, on post-treatment viral control.

**Methods:**

RIO is a randomised, placebo-controlled, double-blinded prospective phase II study. Eligible individuals will have started ART within 3 months of primary HIV infection and have viral sequences that appear to be sensitive to both bNAbs. It will randomise 72 eligible participants 1:1 to the following arms via a two-stage design. In Stage 1, arm A participants are given dual long-acting (LS-variants) bNAbs infusions, followed by intensively monitored Analytical Treatment Interruption (ATI) (*n* = 36); in arm B, participants receive placebo infusions followed by ATI. The primary endpoint will be time to viral rebound within 36 weeks after ATI. Upon viral rebound, the participant and researcher are unblinded. Participants in arm A recommence ART and complete the study. Participants in arm B are invited to restart ART and enroll into Stage 2 where they will receive open-label LS bNAbs, followed by a second ATI 24 weeks after. Secondary and exploratory endpoints include adverse events, time to undetectable viraemia after restarting ART, immunological markers, HIV proviral DNA, serum bNAb concentrations in blood, bNAb resistance at viral rebound, and quality of life measures.

**Discussion:**

The two-stage design was determined in collaboration with community involvement. This design allows all participants the option to receive bNAbs. It also tests the hypothesis that bNAbs may drive sustained HIV control beyond the duration of detectable bNAb concentrations. Community representatives were involved at all stages. This included the two-stage design, discussion on the criteria to restart ART, frequency of monitoring visits off ART, and reducing the risk of onward transmission to HIV-negative partners. It also included responding to the challenges of COVID-19.

**Trial registration:**

The protocol is registered on Clinical.trials.gov and EudraCT and has approval from UK Ethics and MHRA.

**Supplementary Information:**

The online version contains supplementary material available at 10.1186/s13063-022-06151-w.

## Administrative information

Note: the numbers in curly brackets in this protocol refer to SPIRIT checklist item numbers. The order of the items has been modified to group similar items (see http://www.equator-network.org/reporting-guidelines/spirit-2013-statement-defining-standard-protocol-items-for-clinical-trials/).

**Table Taba:** 

Title {1}	The RIO trial: Rationale, design, and the role of community involvement in a randomised placebo-controlled trial of antiretroviral therapy plus dual long-acting HIV-specific broadly neutralising antibodies (bNAbs) in participants diagnosed with recent HIV infection - Study protocol for a two-stage randomised trial
Trial registration {2a and 2b}.	EUDRACT Number: 2019-002129-31 Registered 26^th^ September 2019 ISRCTN Number / Clinical trials.gov Number: NCT04319367 https://clinicaltrials.gov/ct2/show/NCT04319367?term=NCT04319367&draw=2&rank=1 Registered 24^th^ March 2020
Protocol version {3}	Protocol Version 5.0 Date 19/10/2021
Funding {4}	This research is funded by the Bill and Melinda Gates Foundation, [name].

## Introduction

### Background and rationale {6a}

Antiretroviral therapy (ART) has dramatically improved survival for people living with HIV, preventing both disease progression and onward transmission. ART alone cannot cure HIV infection due to viral persistence in an inaccessible reservoir of latently infected cells [1]. Also, drawbacks to current ART include adherence requirements (usually to daily oral medication) and uncertain long-term safety profiles. These factors may contribute to the stigma and discrimination that limits social relationship, including vulnerability to legal action and a reduced quality of life, that are commonly faced by HIV-positive people [2]. The need for repeat drug refills and challenges to drug stock outs in low- and middle-income countries (LMIC) where most HIV-positive people live, also drives the need for alternative approaches to long-term HIV management.

Recent advances in long-acting broadly neutralising antibodies (bNAbs) to HIV *env* protein have shown promise in addressing these issues. Neutralising antibodies prevent pathogens from infecting host cells, by blocking virus entry through disrupting virus-receptor interaction, antibody-dependent cell-mediated cytotoxicity (ADCC), and effector cell-derived soluble factors inhibiting viral spread [3, 4]. There is an additional postulated mechanism whereby the antibodies induce HIV-specific CD8 mediated cellular immune responses similar to a vaccine effect [5]. Neutralising antibodies have been found in the course of natural infection in people with chronic HIV infection [6]. However, only 1% of them develop broad and very potent neutralising bNAb responses that can neutralise a wide range of HIV-1 variants due to the virus’s complex diversity and high mutation rate, and initial attempts to produce them ex vivo showed limited potency [7]. The development of high-throughput neutralisation assays and single-cell antibody cloning techniques have led to second-generation bNAbs with greater potency and breadth [8].

ATIs are a recognised strategy for HIV research to understand the HIV reservoir dynamics and validate strategies for long-term ART-free viral suppression, until biomarkers to predict post-treatment viral control become available. Consensus recommendations for the ethical conduct of trials involving ATI were agreed by a panel of experts on HIV research in 2018 [13], and we further explore the benefits and risks of ATI trials in the discussion later in this manuscript.

In this paper, we describe the methods of the RIO trial. The RIO trial aims to investigate the use of a novel combination of long-acting broadly neutralising antibodies 3BNC117-LS and 10-1074-LS in participants who initiated ART early during primary HIV infection (PHI), in preventing HIV viral rebound after stopping ART for an extended period. We also describe the impact of the COVID-19 pandemic, the modifications to the trial protocol as a result, and the key role of community contribution throughout the study design, management, oversight, and adaptation to the COVID-19 pandemic measures.

### Objectives {7}

#### Primary objective

To determine the efficacy of dual bNAb infusion of 10-1074-LS and 3BNC117-LS at sustaining virological control within 36 weeks following initial ATI compared with placebo infusion.

#### Secondary objectives

To evaluate the safety of dual bNAb infusion of 10-1074-LS and 3BNC117-LS.To determine the role of viraemia at the time of bNAb administration in subsequent virological control.To determine the contribution of circulating bNAbs to virological control compared with a sustained impact following antibody elimination.To document the experiences and determine the attitudes of participants to the interventions and the treatment interruption.

#### Tertiary objective

To determine the mechanisms by which bNAbs infusions can induce sustained virological control after stopping ART.

### Trial design {8}

The RIO study is a randomised, placebo-controlled double-blind two-arm prospective phase II trial in two stages, summarised in Fig. 1. All parties blinded are listed later in this paper under ‘Who will be blinded {17a}’.

**Fig. 1 Fig1:**
[figure not shown]
Summary of trial design

#### Stage 1—72 individuals

##### Arm A

Recruit 36 individuals.bNAbs given once followed by ATI 2 days later.ATI stage up to viral rebound or end of study.Restart ART and follow-up for 16 weeks or to end of study.

##### Arm B

Recruit 36 individuals.Placebo infusion given once followed by ATI 2 days later.1st ATI stage up to viral rebound or end of study.

#### Stage 2—36 individuals from Stage 1 arm B

Restart ART, with immediate bNAb infusion followed by washout period of 24 weeks.2nd ATI up to viral rebound or end of study.Restart ART and follow-up for 16 weeks or to end of study

## Methods: participants, interventions, and outcomes

### Study setting {9}

The target study population include eligible and consenting people living with HIV who commenced ART during confirmed PHI and who have remained with viral suppression below the level of detection (< 50 copies HIV RNA/ml) for at least 1 year. Clinical care will be provided through the National Health Service (NHS). Research study visits will be undertaken at one of the clinical sites in accordance with the trial protocol, all within the UK. Clinical sites are listed in Appendix 1.

All intervention study visits (involving infusions of bNAbs or placebo) will take place at the NIHR Imperial Clinical Research Facility (ICRF) at Hammersmith Hospital, London, UK.

### Eligibility criteria {10}

#### Inclusion criteria

Aged ≥ 18 to ≤ 60 years old at screening.Able to give informed written consent including consent to long-term follow-up.Willing and able to comply with visit schedule and provide blood sampling.Started ART within a maximum of 6 months of estimated date of primary HIV infection, based on one of the following six criteria:
Positive HIV-1 serology within a maximum of 24 weeks of a documented negative HIV-1 serology test result (can include point of care test (POCT) using blood for both tests). The estimated time of infection is taken as the midpoint between the dates of the negative HIV-1 serology or POCT test and positive HIV test at diagnosis, unless there was clear evidence for a transmission event, in which case that date will be taken.The date of a positive p24 antigen result and a negative HIV antibody test.The date of a negative HIV antibody test with either detectable HIV RNA or proviral DNA.Recent infection testing algorithm (RITA) reported as ‘Incident’ confirming the HIV-1 antibody avidity is consistent with recent infection (within the preceding 16 weeks). The estimated date of infection is assumed to be 2 months prior to the date of the incident test result.The date of a weakly reactive or equivocal 4th-generation HIV antibody antigen test.The date of an equivocal or reactive antibody test with less than 4 bands on western blot.Stable on ART with suppressed undetectable HIV viral load (VL) ‘target not detected’ using local assays for ≥1 year.No evidence of viral insensitivity to either 10-1074 or 3BNC117 antibodies based on proviral sequencing algorithm.Hepatitis B virus (HBV) surface antigen or HBV DNA, hepatitis C virus (HCV) Ag or HCV RNA negative or HCV anti-core antibody negative.No significant comorbidities.Nadir CD4 > 350 cells/μL.Current CD4 count > 500 cells/μL or CD4:CD8 ratio > 1.On integrase inhibitor (INSTI) or boosted protease inhibitor (bPI)-based regimen at time of randomisation, if previously on non-nucleoside reverse transcriptase inhibitor (NNRTI) has switched at least 4 weeks prior to randomisation.Adequate haemoglobin (≥120 g/L for males, ≥110 g/L for females).Weight ≥ 50 kg.Females capable of becoming pregnant must agree to use hormonal contraception, intrauterine device, intrauterine hormone-releasing system, or to complete abstinence from at least 2 weeks before the first bNAb/placebo infusion and for 20 months after the last bNAb infusion.Participants must have been vaccinated against coronavirus (COVID-19), at least 4 weeks prior to enrolment.

#### Exclusion criteria

Previous ischaemic heart disease (ST or non-ST myocardial infarction, QRISK3 10-year cardiovascular risk > 20%, stable angina, unstable angina, stroke)Any current or past history of malignancy, excluding squamous cell skin cancers.Concurrent opportunistic infection or other comorbidity or comorbidity likely to occur during the trial, e.g. malabsorption syndromes, autoimmune disease.Any contraindication to receipt of British HIV Association (BHIVA) recommended combination antiretrovirals [14].HTLV-1 co-infectionSARS-Cov-2 infection confirmed by SARS-Cov-2 RT-PCR positive result from nasopharyngeal swab up to 72 h prior to randomisation/dosing visit.Individuals at high risk from severe COVID-19 disease who may be defined in accordance with National Health Service England guidance [15] as vulnerable and shielded (as per the view of participant’s physician)Current or planned systemic immunosuppressive therapy (inhaled or topical corticosteroids are allowed.)Participation in any other clinical trial of an experimental agent or any non-interventional study where additional blood draws are required; participation in an observational study is permitted.History of anaphylaxis or severe adverse reaction to antibody infusions, or hypersensitivity to 3BNC117-LS or 10-1074-LS or to or any constituent products or excipientsTreatment with intravenous immunoglobulin or other monoclonal antibody treatments planned during the duration of the trial.Clinically significant abnormal blood test results at screening including:
Moderate to severe hepatic impairment as defined by significant liver impairment with evidence of advanced fibrosis or cirrhosis with decompensation.Alanine transaminase (ALT) >5× upper limit of normal.Estimated glomerular filtration rate < 60 ml/min/kg.Urine protein creatinine ratio > 30 mg/mmol.International normalised ratio (INR) > 1.5.Physical examination findings: Evidence of organ dysfunction or any clinically significant deviation from normal in physical examination and/or vital signs that the investigator believes is a preclusion from enrolment into the study.Active alcohol or substance use that, in the Investigator’s opinion, will prevent adequate adherence with study requirements.Insufficient venous access that will allow scheduled blood draws as per protocol.Concern regarding likelihood of participant not taking precautions to prevent HIV transmission during treatment interruption period.Pregnancy or breastfeeding

### Who will take informed consent? {26a}

Potential participants will be approached directly by their usual HIV clinician at their clinical site, or by investigators working on the HEATHER cohort study. The HEATHER study is an observational cohort of individuals with documented PHI who commenced on immediate ART within 3 months of HIV acquisition and are invited to have research blood samples taken at regular intervals timed with their regular clinic visits. The cohort has recruited over 350 individuals with treated PHI and acts as a platform for further research studies such as the RIO study (Approved by West Midlands – South Birmingham Research Ethics Committee reference 14/WM/1104).

Those interested in joining the study will be offered an appointment with a Good Clinical Practice (GCP) trained member of the research team. Individuals will then be informed of the details of study and invited to participate, with informed consent given by participants to research staff who are suitably qualified and have been authorised to do so by the CI/Principal investigator (PI) according to GCP guidelines.

### Additional consent provisions for collection and use of participant data and biological specimens {26b}

Consent for the use of blood samples in future research and to transfer samples outside of UK and EU countries will also be obtained.

The participant will be given a minimum of 24 h and the opportunity to question the Investigator, their GP, or other independent parties to decide whether they will participate in the study. Written Informed Consent will then be obtained by means of participant dated signature and dated signature of the person who presented and obtained the informed consent.

## Interventions

### Explanation for the choice of comparators {6b}

The RIO trial design aims to answer two important research questions;
To determine time to viral rebound following one infusion of dual bNAbs compared with placebo. This will inform the field to quantify the impact of the intervention on ART-free viral control. This is the first study to address this research question.To determine if receiving dual bNAbs at the time of ART restart following an ATI can confer post ART viral control after 6 months of ART, at a point when it is anticipated that plasma concentration of bNAbs will be below therapeutic levels.

The second aspect of the trial will explore the scientific question as to whether the lasting impact of dual bNAb treatment affects immune function and whether the ‘vaccinal’ effect of stimulating HIV-specific CD8+ and NK cell activation sufficiently to contain viral replication is a true in vivo phenomenon. Additionally, such is the interest and support from the community representatives that they were very supportive of this two-step design as it enables all eligible interested study participants to receive bNAb.

Comparators for participants receiving the intervention in arm A are participants meeting the inclusion criteria who are randomised into arm B and receive a placebo infusion followed by subsequent ATI.

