### Outcomes {12}

The primary endpoint is the comparison of time to viral rebound within 36 weeks after initial ATI, during Stage 1, summarised by hazard ratios.

Secondary endpoints, for both stages 1 and 2, are:
Safety defined as the number and types of adverse events (AEs) and serious adverse events (SAEs) by groupLength of time undetectable in days following ATI in the absence of detectable ART (comparing arm A vs B and arm B Stage 1 ATI vs Stage 2 ATI), summarised by mean.CD4 T cell counts and CD4:CD8 ratios at weeks 12-, 24-, 36-, and 48-week post randomisation, and 12-weekly until the end of study participation by arm, summarised by median.Percentage of participants with undetectable VL at week 12, 24, 36, and 48 post randomisation (Stage 1; arm A vs B) and then for arm B participants post second ATIQuantitation of proviral HIV DNA and cell-associated RNA at baseline and following viral rebound and resuppression on ART by arm.Duration of remission analysed under multiple alternate definitions (e.g. VL < 40 copies/mL, < 400 copies/mL, < 1000 mL), comparing arm A vs B and arm B Stage 1 ATI vs Stage 2 ATI, summarised by mean.Time to restarting ART after start of ATI, comparing arm A vs B and arm B Stage 1 ATI vs Stage 2 ATI, summarised by median.Time to undetectable HIV VL after restarting ART, comparing arm A vs B and arm B Stage 1 ATI vs Stage 2 ATI, summarised by median.The proportion of participants with detectable ART levels in blood during ATI, at weeks 12, 24, 36, and 48 post randomisation, by arm.bNAb concentration in blood at dosing, weeks 2, 4, 8, 12, 24, 36, and 48, time of viral rebound, and end of study, summarised by mean.Proportion and description of bNAb resistance/sensitivity at pre and post infusion time-points, by arm.Descriptive changes in reported HIV Quality of Life measures at baseline, 2 weeks after infusion, and at the end of study [21].

Tertiary or exploratory endpoints, for both stages 1 and 2, will include:
HIV-specific (humoral and cell-mediated) and innate immune responsesImmune phenotyping and activation/exhaustionHost gene expressionViral sequence and integration site analysisMeasures of the HIV viral reservoir in CD4+ T cells.

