### Sample size {14}

#### Sample size and power considerations

Stage 1—arm A compared to arm B

Underlying viral rebound rates at 36 weeks of 90% and 55% in the control and intervention groups respectively (i.e. 10% and 45% free from rebound by 36 weeks; hazard ratio 0.35) will be detected with 90% power using a two-sided log-rank test at the 5% significance level provided there are 31 participants per arm and no loss to follow-up or return to ART treatment prior to 36-week primary outcome. We propose to recruit 72 participants in order to provide an allowance of approximately 10% return to ART treatment, and loss to follow-up, prior to the earlier of either 36 weeks or a primary event.

Stage 2—arm B only

For patients in arm B, we will look at the within-person difference in ‘length of time undetectable (in days)’ between first and second period. Assuming a standard deviation of 14 days and a conservative correlation between the number of days in the first and second period of 0.7, 36 patients will allow detecting a difference of 6.6 days between the two periods with 90% power and two-sided alpha 0.05, including 15% dropout rate.

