### Benefits of the study

This randomised phase II study will determine whether a combination of dual long-acting bNAb may result in sustained HIV suppression in the absence of ART amongst individuals with immune recovery treated since primary HIV infection.

The study design allows the testing of two hypotheses, the first being that combination long-acting bNAbs will result in a sustained and quantifiable period of viral control following ATI compared with placebo amongst a specifically selected group of individuals who started ART in primary HIV infection.

The second hypothesis that bNAbs may drive sustained HIV control beyond the duration of detectable bNAb concentrations, through processes mediated by the host innate immunity. This is based on evidence that HIV may be controlled in the absence of antiretroviral therapy, in individuals often termed ‘elite controllers’, and this control is mediated by highly potent HIV-1-specific CD8 T cells [5]. In macaque SHIV models, depletion of CD8 T cells resulted in loss of viral control in monkeys who were virally suppressed following 3BNC117 infusions, suggesting CD8 T cells are responsible for control of virus replication in controller macaques. This process is possibly driven by formation of immune complexes from low levels of progeny virions prior to viral rebound, compared to the near complete inhibition of virus replication by ART limiting the amount of viral antigen to induce immunity [35]. It is unclear if similar CD8 T cell responses in humans may be elicited by bNAbs, and the role of ATI for providing the initial antigen production to drive this response [4]. This two-stage study design allows the investigation of this hypothesis, providing significant virological and immunological insights into bNAb-mediated viral control mechanisms that determine HIV control and remission. Early and continued community involvement throughout the study design and management will encourage stronger participant satisfaction and person-centred outcomes for the community of people living with HIV.

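### Stage 2 is described as testing a bNAb effect, but its only contrast, arm B's second ATI against its own first in fixed order, cannot separate bNAbs from order and background.

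*Protocol article*

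**What the plan says.** The section Explanation for the choice of comparators {6b} sets two research questions. The second is "To determine if receiving dual bNAbs at the time of ART restart following an ATI can confer post ART viral control" once 6 months of ART have passed, when bNAb levels are expected to be sub-therapeutic. The section names a comparator for arm A (randomised placebo) and none for this second question. The Discussion paragraph of the Abstract and Benefits of the study both say the design tests whether bNAbs sustain control after they are no longer detectable.

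The Stage 2 sequence is the same for everyone in it: "Restart ART, with immediate bNAb infusion followed by washout period of 24 weeks", then a second ATI. The comparator appears under Outcomes {12} as "arm B Stage 1 ATI vs Stage 2 ATI". The Stage 2 sample size says: "we will look at the within-person difference in ‘length of time undetectable (in days)’ between first and second period". Statistical methods {20a} assigns a paired t-test or another paired approach, and Interim analyses {21b} confines this analysis to arm B.

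**The concern.** A question about what bNAbs given at ART restart add to a later interruption needs a second ATI with bNAbs set against a second ATI without them. Here every participant contributes the placebo period first and the bNAb period second. Anything else that changes between the periods moves the paired difference exactly as a bNAb effect would.

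What is at stake is the Stage 2 conclusion. A significant paired difference could come from bNAbs, from order or background, or from both. A real bNAb effect could also be hidden by a period effect in the opposite direction.

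**Working it through.** **The two periods side by side**

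| | First ATI (arm B) | Second ATI (arm B) |
|---|---|---|
| Infusion | Placebo, shortly before the ATI | bNAbs around ART restart, 24 weeks before the ATI |
| Latest spell of ART | At least 1 year, suppressed without interruption (Inclusion criteria; Recruitment {15}) | About 24 weeks, restarted after rebound |
| Earlier ATI and rebound | None in this trial | Yes |
| Blinding | Double-blind (Who will be blinded {17a}) | Open (Sequence generation {16a}) |

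These differences all change together and in the same direction of time for every participant. Arm A cannot supply the missing contrast, because it restarts ART and has no planned second ATI. The only other repeat interruption mentioned is a case-by-case one after SARS-CoV-2 infection, which is not a planned comparator.

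**Reproducing the plan's figure**

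Inputs from Sample size {14}, Stage 2: SD 14 days, correlation 0.7, 36 participants, 15% dropout, two-sided 5%, 90% power, difference 6.6 days.

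1. SD of the paired difference = 14 × √(2 × (1 − 0.7)) = 14 × √0.6 = 10.84 days.
2. Evaluable pairs = 36 × 0.85 = 30.6, so 30 or 31.
3. Standard error with 30 pairs = 10.84 / √30 = 1.98 days.
4. Power at 6.6 days by noncentral t = 89.6% with 30 pairs and 90.6% with 31. The difference detectable at 90% power is 6.64 or 6.53 days.

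The stated 6.6 days reproduces. The sizing is not in dispute.

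**What the paired test responds to**

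Let B be the bNAb effect and P the combined effect of order and background, both in days. The expected paired difference is B + P, and the rejection probability depends only on that sum. The documents give no value for P, so the shifts below are assumptions. Each row is the plan's own power curve with B = 0 and 30 pairs.

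| Assumed P (days) | P / 1.98 | Probability of a significant result |
|---|---|---|
| 0 | 0 | 5% |
| 2 | 1.01 | 16% |
| 3 | 1.52 | 31% |
| 4 | 2.02 | 50% |

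With 31 pairs the last three are 17%, 32% and 51%.

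In the opposite direction, if B = 6.6 and P = −2, the expected difference is 4.6 days and power falls from 90% to 61%. If P = −3.3, it is 3.3 days and power is 36%.

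More participants would not help. The standard error shrinks, but the quantity estimated is still B + P.

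**The case against.** The design is deliberate and disclosed. It was chosen with community representatives so that all participants could receive bNAbs, and a bNAb-free second ATI would work against that. Stage 2 is secondary, and several sections describe it as exploring the question. The vaccinal hypothesis also draws on bNAb concentrations and on T-cell, NK-cell and reservoir assays, so the paired test is not the only evidence. The analysis plan, not shown here, may temper the interpretation. All of this stands, and it is why no new arm is asked for. It does not remove the stronger wording in the three places named, the 90% power statement, or the fact that no analysis plan can recover a contrast the design lacks.

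Some stronger readings are tempting but unsupported:

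- **That the protocol itself predicts an order effect without bNAbs.** Benefits of the study mentions "the role of ATI for providing the initial antigen production to drive this response", but the response meant there is a CD8 response elicited by bNAbs. Risk of undertaking ATI lists reservoir growth on rebound as a risk, then cites evidence against it in people treated early.
- **That participants have had far less suppression before the second ATI.** The comparison of 24 weeks with at least 1 year covers only the latest spell. The same people also carry the earlier suppression.
- **That open-label treatment biases the sized outcome directly.** Viral load is a laboratory measure. Knowledge of treatment matters mainly through elective ART restart, which is allowed at any viral load, and through extra visits.

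**Conclusion.** The point holds as a mismatch between claim and design. bNAb exposure in Stage 2 is completely aliased with period, so the planned paired test cannot determine whether bNAbs caused a difference. This follows from the fixed sequence and rests on no numerical assumption.

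The figures of 16%, 31% and 50% are illustrations. They rest on assumed shifts of 2, 3 and 4 days together with the plan's SD, correlation and dropout. A reader might take them as the expected false-positive rate of Stage 2. They are not, because neither the existence, the direction nor the size of a period effect can be learned from the documents. Nor do the documents say that a significant paired difference alone would be reported as a bNAb effect; they leave room for that reading and state no limit on it. The randomised Stage 1 comparison, including the primary endpoint, is unaffected.

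**What to change.** 1. In the Abstract (Discussion), Explanation for the choice of comparators {6b} and Benefits of the study, describe Stage 2 as an uncontrolled, fixed-order, within-person comparison that estimates bNAb and period effects combined.
2. State that a significant paired difference alone will not be reported as a bNAb effect.
3. Treat the Stage 1 versus Stage 2 comparison of time to restarting ART as descriptive, because one period is blinded and the other open.

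Optionally, report the paired difference by viral suppression at the start of the second ATI. This is supportive description only. Suppression at that point is measured after bNAb exposure, so conditioning on it neither removes the confounding nor supplies the missing contrast.

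The cost is a few sentences and a more modest Stage 2 claim. Treatment, schedule and sample size do not change, and access to bNAbs for all participants is kept.
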